## Sub-study 2 Inclusion/Exclusion Criteria

Inclusion*:*

- Be a male aged 25-39
- Resident of one of the 45 study Locations
- Already enrolled in TASCO study (Main study)
- Has declined HIV testing
- Has consented to unlinked testing of his blood from the bleeding vessels/finger prick
- Sought services at a participating VMMC clinic.

Exclusion*:*

- Males outside the 25-39 age bracket
- Non-resident of one of the 45 study Locations
- Not enrolled in TASCO study
- Has accepted linked HIV testing
- Has not consented to unlinked testing of his blood from the bleeding vessels/finger prick.

## Enrollment of Sub-study Participants:

Participants for sub-study 3 will be enrolled from all the 45 Locations; however the Locations will be randomly assigned into nine (9) groups each with five clusters. Leaving the first two weeks to allow for the study set up and, have it up and running smoothly, and the last month for close out, enrollment into the study will take place over the remaining four and a half months (18 weeks). The first group will be assigned the first two weeks (i.e. week 3 & 4) to enroll the first 16 consenting participants; the next group of five clusters will be assigned the next two weeks (i.e. week 5 & 6) to enroll their participants and the process repeated until all the 45 clusters have been assigned their two-week enrollment period (ending week 19 & 20). After this period, enrollment will be opened for a further two weeks to all the clusters who will not have achieved the enrollment target. We believe that since each Location will be enrolling only 16 participants, the proposed arrangement allows for adequate time to enroll all the sub-study 3 participants and for enrolment to spread throughout the data collection period.

## Methods/Procedure:

We will perform unlinked testing of blood from bleeding vessels of those whose HIV status is unknown. While the call for proposals recommended testing blood from the excised foreskin, we are concerned that we may not be able to harvest sufficient blood from most foreskins to perform the test. This is because the forceps-guided method being used in Kenya^[[31]](#endnote-30)^ crushes the foreskin and compresses the blood vessels that supply the distal section. This results in little or no bleeding on the excised foreskin. We therefore propose to only collect blood samples from the bleeding vessels from participants (n=700).

We will also offer participants in this sub-study, the option of collection their Dried Blood Spot (DBS) blood samples from a finger prick. For participants who consent to unlinked HIV testing from bleeding vessels, the DBS sample will be collected during surgery. For participants who consent to unlinked HIV testing from finger pricking, the sample will be taken after surgery is completed but while the participant is still in the theatre. The surgeons and their assistants will be trained on both methods of blood collection (Dried Blood Spot and finger prick). The finger prick sample will be for DBS test and not be for rapid HIV test.

- - - 1. DBS Sample from Bleeding Vessels:

In a circumcision procedure, there are typically about 5 – 6 bleeding vessels, a result of the severance of the superficial vessels supplying the distal portions of the foreskin. Bleeding (generally minimal with good control) is usually stopped by ligation or cauterization. Immediately after excision of the foreskin, the raw area is exposed and the process of hemostasis is started. This is usually done by application of pressure around the raw area using dry and sterile gauze and helps to close up capillaries that may cause oozing of blood. This is followed by identification and clumping of individual bleeding vessels using haemostatic artery forceps. This step is usually done by the surgeon with the help of an assistant surgeon whose role is to swab and clear the surgical field to aid in the identification of the blood vessels. During this stage, the assistant will harvest a few drops of blood using the micro-capillary tube from one of the bleeding vessels prior to its clumping by the surgeon. After clumping of all the bleeding vessels, they are ligated using chromic catgut. The process of clumping and ligation of the bleeding blood vessels takes up to 3 minutes. The assistant surgeon will harvest blood samples from the bleeding vessel on the opposite end from where the surgeon starts to clump the first bleeding vessel. The actual process of sample collection will take less than one minute.

VMMC surgeons or their assistants will use capillary tubes to collect blood from the bleeding vessels and put directly on the blotting paper as described below. Details of the sample collection, preparation and laboratory procedures as well as SOPs are attached as Appendix 26 A & B which cover sample collection, preparation, laboratory procedures and SOPs for Unlinked HIV Testing.

Steps for DBS Sample from Bleeding Vessels:

1. Using heparinized capillary tubes, collect blood from the bleeding vessels immediately after circumcision
2. Fill the capillary tubes to almost ¾ with blood
3. Add 2 drops (50 µL) of blood in each circle of DBS sample collection card
4. Repeat procedure 3 until all the circles are completely filled.
5. Inspect card to ensure you have collected enough blood, and the specimen is valid
6. Place DBS sample collection card on a horizontal clean dry surface to **AIR DRY** for at least 3 hours
   - - 1. Procedure for DBS Sample from Finger Prick:
7. Let participant choose a finger to be pricked, preferably any of the three middle fingers.

Should they change their minds about knowing their HIV status, participants will have the option to obtain their HIV test results for up to one year following the date of the collection of the blood sample. Since the HIV testing will be done off-site (at the KEMRI/CDC laboratory), after consenting we will give each participant a slip of paper with his sample number and a telephone number that he can use to call and ask for his HIV test results. A Laboratory Technologist will be engaged by the study and trained to release results to any participant who calls to get his results. This person will be located off-site and will not be directly linked to the participants or the field staff who collect, label and ship the samples. In addition, given that the samples will not contain any identifiers, the Laboratory Technologist will not be able to link the test results to a participant. These measures will ensure that anonymity of participants is observed as initially planned. To verify that the person calling is the participant, the Laboratory Technologist will ask the caller for the month that the participant was circumcised and the name of the site where the circumcision took place. The sample number will be non-sequential random numbers. The sample numbers will not be linked or related to any numbers in the participant’s Participant Unique ID number used in the main study. Consequently if a participant loses this unique code, he will not be able to get his test results.

**Note:** The clinic staff obtaining specimens will not have access to the laboratory where the test will be done; similarly, the laboratory staff will not have access to the clinic records or meet the participants.

***Steps to follow when samples arrive at CDC/KEMRI Laboratory:***

1. Drivers or messengers shall deliver the samples from IRDO field stations to CDC HIV-R Laboratory weekly.
2. The samples shall be received by IRDO’s Lab staff, who will verify their state and accompanying request/delivery forms (e.g. labeling) and document in the specimen receiving book.
3. The samples shall be tested for HIV using CDC HIV-R Laboratory Specific SOPs as described under methods above and in the attached sample collection, preparation, laboratory procedures and SOPs (Appendices 26 A & 26 B).
4. The results shall be sent as a password-protected attachment from CDC HIV-R Laboratory to IRDO study Data Manager by email immediately they are ready (1 to 2 days for negative or positive results and one week for discordant results).

The results of this testing will affect future VMMC counseling for men who refuse testing. For example if the HIV rate among these men is significantly higher, then moving forward these males will receive increased counseling regarding the importance of testing, the lack of HIV prevention benefit if already HIV infected and they do not know, and the importance of condom use.

## Laboratory Procedure:

*Sample collection, Preparation, Laboratory procedures and SOPs for HIV testing* are attached as Appendix 26 A & B and include the following:

1. Preparation, Storage, Transportation and Processing of DBS for HIV Elisa Testing – Appendix 26 A
2. CDC HIV ELISA SOPs **–** Appendix 26 B

***Method validation***: We shall use DBS for HIV Elisa Testing under laboratory conditions, as described above and detailed in Appendix 26. KEMRI/CDC laboratory is ISO 15189 accredited and all the methods in the laboratory have been validated and operate as per the ISO standards (SOP for Method Validation is available in the KEMRI/CDC laboratory for reference).

***Biosafety training of study staff:*** All IRDO staff engaged in VMMC service provision are trained and experienced Clinical Officers (COs), Nursing Officers (NOs) and Infection Prevention Officers Thus, they are already trained on biosafety methods, with topics covering: precautions for collecting specimens; handling spills and accidents; handling and disposal of contaminated materials and waste; selection and care of gloves; sterilization and disinfection of medical equipment, etc. The COs and NOs will be trained on sample collection for HIV testing while biosafety refresher training for Lab staff will cover procedures for HIV testing and other topics above, as relevant.

**Disposal of testing materials:** The specimens obtained will be used only for Laboratory HIV testing in KEMRI/CDC laboratory, and once the results are out, the specimens will be immediately discarded and will not be used for any other purpose. Testing materials and other bio-wastes will be disposed of according to the MOH/WHO guidelines for VMMC service provision^37^. All our program staff are already trained on these guidelines and routinely dispose of such wastes. IRDO has a robust Quality Assurance/Quality Control system in place that provides routine monitoring of quality of VMMC and other clinical services. Our staff are also periodically supervised to ensure compliance with the WHO/MOH guidelines by internal and external experts (including those from the national and provincial MOH headquarters, as well as those from the local and international PEPFAR, CDC, USAID and DOD offices).

**COSTING VMMC IN THE CONTEXT OF THE INTERVENTIONS (SUB-STUDY 3)**

Study Design: One of the aims of the study is to determine the cost of demand creation, as well as the unit cost of providing VMMC services under each of the demand creation strategies being proposed. Data on costing will be collected across all the study arms. Whereas economic evaluation of service delivery has been conducted in several contexts ^[[32]](#endnote-31)^ there is limited information on cost-effectiveness of various approaches used for recruitment to increase service uptake. We plan to assess the cost-effectiveness of demand creation for VMMC services based on the three interventions. The results will demonstrate the accrued costs and net savings associated with each intervention strategy. This information will support policy and program decisions, guideline formulation, and allocation of scarce resources to scale up effective demand creation approach(es).

Methods:

The primary outcome of the main study is the incremental change in circumcisions performed attributable to the respective demand creation interventions. Costs will be estimated for primary outcome with reference to the control group, in which we will continue to provide routine recruitment approaches. This will demonstrate how the costs vary depending on the mode of demand creation.

We shall adopt a societal perspective because of the ability to integrate diverse factors into the model and the role the public sector plays in HIV prevention and management. This approach incorporates all costs borne by the implementers in recruiting participants for services.

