**Methods:** We will employ cluster-randomized controlled design. Through elimination by factors such as proximity to circumcising communities, multi-ethnic urban populations, and geographical proximity to each other, 45 administration Locations in Nyanza Province have been selected and randomized into IPC implemented alone, DSO implemented alone, IPC and DSO implemented together and control. Under IPC, we will develop a Toolkit for Addressing Barriers and Facilitators to VMMC with messages that address barriers to and reinforce facilitators of VMMC, and engage behavioral counselors to deliver intervention massages that are custom-made to address participants’ specific issues; Under DSO, selected facilities, days and hours will be set aside to serve only men aged ≥25 years; these sites will be served by older, male providers only; Under Combined IPC and DSO, the effect of both interventions implemented together will be examined; and in the Control locations, no intervention will be implemented. Altogether, 4,932 men aged 25-39 years are expected to take up VMMC during the study period, which will take up to nine months.

For aim 2, we will collect blood samples from bleeding vessels of an estimated 700 men whose HIV status is unknown, and perform unlinked test for HIV at the KEMRI/CDC HIV Laboratory in Kisumu. For aim 3, we propose to extract from our procurement, stores and accounts records expenditures for demand creation and service delivery.

To augment this study, we will nest a sub-study (sub-study 4) in all the 45 study Locations and enroll approximately 720 men who are in stable sexual relationships, together with their partners, for post circumcision follow up visits to monitor the impact of involving female partners on time to resumption of sex post-surgery.

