Justification: HIV testing and counseling is one of the components of comprehensive VMMC services recommended by the World Health Organization and the Government of Kenya. However, our program data indicate that testing currently stands at about 74%, and questions arise if those who decline testing could have higher prevalence than those accepting to be tested. While VMMC is not denied to those who test positive for non-HIV prevention reasons, counseling messages for those known to be HIV infected differ from those who are HIV-negative. It is therefore important to compare HIV prevalence among those who opt to know their HIV status and those with unknown status to provide information that will inform counseling messaging among the latter group.

We will perform the testing of blood from bleeding vessels of those of unknown HIV status. The samples will be sent for testing at the KEMRI/CDC Laboratory in Kisumu.

***Aim 3: Determine the cost of providing VMMC among the three interventions relative to each other and to no intervention.***

Justification: Costing of new interventions help in making policy decisions regarding their viability for adoption. Our programs data have indicated that with sufficient demand for services, which we hope to create among older men through the proposed interventions, the cost of VMMC are expected to go down markedly. We will extract uptake data from procurement, stores and accounting records in terms of numbers of MCs done, and identify all expenses that went into each intervention and calculate the unit cost of each demand creation intervention.

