## Sources of costing data

We will collect data from all study sites using a tool adapted from the Male Circumcision Decision-Makers’ Program Planning Tool (DMPPT) ^[[33]](#endnote-32)^ for each of the demand creation strategies (Appendix 22: Costing Instrument). The DMPPT was developed by the USAID/Health Policy Initiative in collaboration with UNAIDS to enable decision-makers to understand the potential cost and impact of various options for scaling up male circumcision services.^28^ The DMPPT has previously been used to undertake costing of male circumcision services in East and Central Africa.^[[34]](#endnote-33)^ We shall use this instrument as our data collection tool to estimate the cost of demand creation and the unit cost of providing VMMC (i.e. cost per adult circumcised) in each of the four study arms.

Table 6 below summarizes the key data sources for the various components of the unit costing tool and the DMPPT.

**Table 6:** Summary of data sources for use in costing

| **Type of Data** | **Source of Data** |
| --- | --- |
| Direct demand creation costs | - Requisitions from the stores to support demand creation. - Payments made by accounts department towards local transport for RAs, production and distribution of IEC materials, road shows, print and electronic media events, and other expenses. - The number of circumcisions done extracted from the VMMC registers. |
| Staffing and compensation | - Cost for hiring and training RAs will be based on actual training expenditure obtained from accounts and HR departments. - For staff involved in recruitment, their salaries, fringe benefits and allowances will be obtained from accounts department. |
| Operational costs | - The operational costs for each VMMC site will be derived from the records at the district level accounts offices. These include rent and utilities, vehicle insurance and maintenance, and communication costs. |
| Administrative and program costs | - We shall apportion the cost of supervision by key staff according to proportionate time spent on study related activities. Costs are salaries, allowances and fringe benefits. Other costs such as external audits, subscription fees to umbrella unions, and payments to statutory bodies shall be apportioned accordingly. |

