| Service provision cost | - Service providers, field supervisors and support staff will be tracked in terms of salaries, allowances and fringe benefits; also, cost of VMMC supplies will be tracked, as well as proportional cost of equipment and instruments |

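### The costing sub-study is declared societal but defined and sourced as implementer costs, so its cost-effectiveness ratios would carry a perspective they do not have

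*Protocol*

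**What the plan says.** The Methods of sub-study 3 name the perspective: "We shall adopt a societal perspective because of the ability to integrate diverse factors into the model". The following sentence says what it contains: "This approach incorporates all costs borne by the implementers in recruiting participants for services".

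The data sources are described in several places:

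- **Abstract, for the costing aim:** "we propose to extract from our procurement, stores and accounts records expenditures for demand creation and service delivery".
- **Study Aims and Justification, same aim:** the team will use those same kinds of records and "identify all expenses that went into each intervention and calculate the unit cost of each demand creation intervention".
- **Table 6, demand creation:** stores requisitions, and "Payments made by accounts department towards local transport for RAs, production and distribution of IEC materials".
- **Table 6, recruitment staff:** "their salaries, fringe benefits and allowances will be obtained from accounts department".
- **Table 6, operations:** "The operational costs for each VMMC site will be derived from the records at the district level accounts offices".
- **Table 6, service provision:** "Service providers, field supervisors and support staff will be tracked in terms of salaries, allowances and fringe benefits", with supplies and a share of equipment and instruments.
- **Data Analysis, costing aim:** expenses of providing the service, such as supplies, personnel, rent and transport, tracked by Location.

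The section on ICER estimation divides incremental cost by incremental effect. The effects include DALYs averted, HIV infections averted and the additional proportion of men reached. The ratios are the key outcome measures and are to be read against willingness-to-pay values.

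**The concern.** A societal perspective counts costs whoever bears them: the programme, the participant, the household and other payers, with any savings to them. A provider perspective counts only what the programme spends. The two adjacent sentences in the Methods give the first label to the second content.

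The label matters because the sub-study says its results should support policy, guidelines and the allocation of resources. A reader who sees a societal ICER will set it beside other societal ICERs, or against a threshold meant for them, and will assume that participants' costs have been counted. The background section itself reports that worry about providing for the household while healing keeps men from circumcision. So the protocol recognises a participant cost that the costing leaves out.

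**Working it through.** The protocol states no cost and no ICER, so there is no figure to reproduce. The check compares the declared label with the cost items, then asks what the missing items would do to each ratio.

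**Step 1: who bears each cost shown.**

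| Place | Cost item | Bearer |
| --- | --- | --- |
| Sub-study 3, Methods | Definition of the approach | Implementer |
| Abstract; Study Aims | Procurement, stores and accounting records | Implementer |
| Table 6, demand creation | Store requisitions, accounts payments; transport is for research assistants | Implementer |
| Table 6, staffing | Hiring, training, payroll | Implementer |
| Table 6, operations | Site costs from district accounts offices | Implementer |
| Table 6, administration | Apportioned supervision, audit, fees | Implementer |
| Table 6, service provision | Provider pay, supplies, equipment share | Implementer |
| Data Analysis, costing aim | Expenses of providing the service | Implementer |
| Sensitivity Analysis | Overheads, service staffing, uncertain resource-use items | No participant cost named |

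No row belongs to the participant, his household or the payer for HIV care. The Methods definition speaks only of recruitment, while Table 6 and Data Analysis also cover service provision. That is a difference of scope, but both are on the implementer side.

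**Step 2: effect on cost per circumcision.** Let an intervention arm have provider cost C1 and N1 circumcisions, and the control arm C0 and N0. Let c be the participant cost per circumcised man, taken as the same in both arms.

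- Average provider cost per circumcision in the intervention arm: C1/N1. Societal: (C1 + c·N1)/N1 = C1/N1 + c.
- Provider cost per additional circumcision: (C1 − C0)/(N1 − N0).
- Societal: (C1 + c·N1 − C0 − c·N0)/(N1 − N0) = (C1 − C0)/(N1 − N0) + c.

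Both ratios rise by exactly c. The protocol gives no value for c.

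**Step 3: effect on cost per infection or DALY averted.** Let ΔN = N1 − N0 be the additional circumcisions, k the infections averted per additional circumcision, and h the care cost averted per infection. Then:

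- ΔC(societal) = ΔC(provider) + c·ΔN − h·k·ΔN = ΔC(provider) + (c − h·k)·ΔN.

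The sign of the change is the sign of c − h·k. The protocol gives none of c, h or k. The study-design text of sub-study 3 promises net savings, but Table 6 names no source for h.

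**The case against.** The case on the other side has real force.

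1. **The aim itself asks for the cost of providing the service.** Implementer costs answer that aim, the components are openly listed, and no stated figure is wrong. This stands: it makes the problem one of labelling and interpretation rather than a failed analysis. It does not remove the contradiction.
2. **Table 6 describes its sources as the key ones, and Appendix 22 is not shown.** An extra item there cannot be excluded. That also stands, but the Methods' own definition would still be of implementers' costs.
3. **A reader might infer that the omission could reorder the arms**, because dedicated outlets offer evening and weekend hours and aim for shorter waits. The documents do not support this. Step 2 shows that an equal cost per man adds the same amount to every arm's cost per additional circumcision. The protocol justifies dedicated outlets mainly by discomfort at queuing with younger clients and at female providers, and it neither claims nor sizes a time saving for participants.
4. **A reader might want to price the gap** from the KSh 324 daily figure under Compensation. That figure is a foreman's minimum wage, not a measure of these men's earnings, and the protocol gives no number of days lost. No amount follows.
5. **A reader might propose adding cost questions to the endline interview.** The Phase 5 criteria exclude men already recorded as circumcised, so most of the men whose costs matter would not be asked. Data Analysis and Table 8 describe a wider endline survey, but that inconsistency would have to be settled first.

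**Conclusion.** The point holds as a mismatch between label and content. As written, the ICERs would be provider (programme) ratios presented as societal. The finding rests on the two adjacent sentences in the Methods and on the absence of any participant, household or averted-care source in the protocol text, with Appendix 22 unseen.

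On size: a true societal cost per circumcision, average or incremental, would be higher by c. This assumes that c is positive and about equal across arms; its value is unknown. It might be inferred that every ICER is therefore too favourable. That goes too far: for infections or DALYs averted, the omitted care savings pull the other way and the net direction is open.

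The consequence is confined to sub-study 3. The trial's comparison of circumcision uptake does not use these costs.

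**What to change.** In the Methods of sub-study 3, replace the societal perspective with a provider (implementer) perspective. Report the ICERs under that label, and compare them only with estimates made from the same perspective.

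This costs a change of wording in the protocol and the same label in the reports. It needs no new data and no change to Table 6.
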